#### Implementation outcomes

We will measure the implementation outcomes at the level of the provider (increase the number of providers giving HPV vaccine recommendations and their confidence in recommending the vaccine to hesitant parents), practice (increase in the number vaccine doses provided per practice and increase in the number of reminders provided to patients for HPV vaccine dose completion), and at the level of the patient/parent (increase parental confidence and reduce perceived barriers in vaccinating their children). We will conduct the HCP/staff and parent surveys 12 months after project activities start. In addition, we will also use the i-PARIHS framework [63] to gather observational data during the implementation period, which will enable us to track and review the progress of each practice.

### Analyses

#### Sample size justification

Based on the 2019-2021 data from three participating FQHCs, the average number of 11-12 year old patients seen per practice is 109 per 3 months, the HPV initiation rate ranges from 24.6% to 40.9% with an ICC of 0.026, and the HPV completion rate ranges from < 1% to 14.7% with an ICC of 0.003. Conservatively, we assume there will be an average of 30, 11–12 year old patients per practice per 3 months. We assume the average HPV initiation rate during the control period varies from 20 to 60% with an ICC of 0.026, and the average HPV completion rate during the control period varies from 3% to 40% with an ICC of 0.003.

A sample of 9 practices (three practices per FQHC) in a custom stepped-wedge design (see Table 3, 0 means control period, “.” means implementation/transition period, and 1 means intervention maintenance period) with 15, 3-month time periods, and an average of 420(= 30 × (15–1)), 11–12 year old subjects per practice with an average of 30 subjects per practice per 3-month (for a total sample size of 30 × (15–1) × 9 = 3,780 subjects) achieves 80% power to detect a minimum difference of 0.094 to 0.118 in initiation rate between the intervention maintenance period (depending on the initiation rate in the control period, see Table 4) and the control period using a two-sided Wald Z-Test, an ICC of 0.026, and a significance level of 0.050 (PASS version 2022). This study design achieves 80% power to detect a minimum difference of 0.039 to 0.112 in the HPV completion rate between intervention maintenance and control periods depending on the completion rate in the control period and the value of ICC of 0.003 (Table 4).

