**Table 3 Tab3:**
[figure not shown]
Custom stepwise design matrix plot

**Table 4 Tab4:** Minimum detectable difference at 80% power using proposed design

Outcome	Intra-cluster correlation coefficient (ICC)	Rate in the control period	Minimum detectable difference at 80% power	Minimum detectable rate in the intervention period
HPV Initiation	0.026	0.2	0.094	0.294
		0.3	0.108	0.408
		0.4	0.116	0.516
		0.5	0.118	0.618
		0.6	0.116	0.716
HPV Completion	0.003	0.03	0.039	0.069
		0.05	0.05	0.1
		0.1	0.069	0.169
		0.15	0.082	0.232
		0.2	0.092	0.292
		0.3	0.105	0.405
		0.4	0.112	0.512

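### Table 4 fixes the outcome variance at the control-period rate, so the claimed 80% power fails at low rates: about 60% at the 3% completion row

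*Protocol article*

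**What the plan says.** The Sample size justification describes "A sample of 9 practices (three practices per FQHC) in a custom stepped-wedge design" over 15 three-month periods. Each practice is taken to contribute 30 patients in a quarter, and the stated total of 3,780 is 30 × 14 × 9. The test is specified as "using a two-sided Wald Z-Test, an ICC of 0.026, and a significance level of 0.050 (PASS version 2022"). For completion, the planning assumption is that "the average HPV completion rate during the control period varies from 3% to 40% with an ICC of 0.003". For initiation, planning uses control rates of 20–60% and an ICC of 0.026, and the text claims 80% power for differences of 0.094 to 0.118. The corresponding claim for completion reads: "This study design achieves 80% power to detect a minimum difference of 0.039 to 0.112 in the HPV completion rate".

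Table 4, titled "Minimum detectable difference at 80% power using proposed design", gives the 12 rows behind those ranges. The text does not say which variance was used. Observed 2019–2021 rates at the three FQHCs are given as 24.6% to 40.9% for initiation and from under 1% to 14.7% for completion. Completion in 11–12 year olds is part of the primary outcome, and the Data collection section on implementation says the trial was powered on initiation and completion.

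**The concern.** Table 4 shows the same detectable difference, 0.116, at control rates of 0.4 and 0.6. The intervention rates are then 0.516 and 0.716, with binomial variances of 0.250 and 0.203. If the intervention-period variance entered the calculation, the two differences should not agree. Equality is what one would see if only p0(1−p0), which is 0.24 in both rows, had been used.

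This shortcut does little harm near 50%, where p(1−p) is flat. At low rates the variance rises steeply with the rate, so an increase in completion brings a clearly larger variance and the shortcut overstates power. The observed completion rates lie in that region. A null completion result would then be read against a power claim that the design does not meet.

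**Working it through.** **Inputs.** From the Sample size justification: two-sided alpha 0.05, power 80%, 9 practices in 3 sequences of 3, 15 quarters, 30 patients per practice-quarter, ICC 0.026 (initiation) and 0.003 (completion). The rates p0 and differences d are from Table 4. The multiplier is 1.960 + 0.842 = 2.802.

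**Step 1: which variance was used.** If the standard error is proportional to √[p0(1−p0)], then d/√[p0(1−p0)] must be constant within each ICC. If the average of the two periods' variances, v̄ = [p0(1−p0) + p1(1−p1)]/2, had been used, d/√v̄ would be constant instead.

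| Outcome | p0 | d | p1 | p0(1−p0) | p1(1−p1) | d/√[p0(1−p0)] | d/√v̄ |
|---|---|---|---|---|---|---|---|
| Initiation | 0.20 | 0.094 | 0.294 | 0.1600 | 0.2076 | 0.235 | 0.219 |
| | 0.30 | 0.108 | 0.408 | 0.2100 | 0.2415 | 0.236 | 0.227 |
| | 0.40 | 0.116 | 0.516 | 0.2400 | 0.2497 | 0.237 | 0.234 |
| | 0.50 | 0.118 | 0.618 | 0.2500 | 0.2361 | 0.236 | 0.239 |
| | 0.60 | 0.116 | 0.716 | 0.2400 | 0.2033 | 0.237 | 0.246 |
| Completion | 0.03 | 0.039 | 0.069 | 0.0291 | 0.0642 | 0.229 | 0.181 |
| | 0.05 | 0.050 | 0.100 | 0.0475 | 0.0900 | 0.229 | 0.191 |
| | 0.10 | 0.069 | 0.169 | 0.0900 | 0.1404 | 0.230 | 0.203 |
| | 0.15 | 0.082 | 0.232 | 0.1275 | 0.1782 | 0.230 | 0.210 |
| | 0.20 | 0.092 | 0.292 | 0.1600 | 0.2067 | 0.230 | 0.215 |
| | 0.30 | 0.105 | 0.405 | 0.2100 | 0.2410 | 0.229 | 0.221 |
| | 0.40 | 0.112 | 0.512 | 0.2400 | 0.2499 | 0.229 | 0.226 |

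The control-variance ratio is constant to rounding in both blocks; the average-variance ratio is not. This step needs no design matrix.

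**Step 2: reproduce the stated figures.** Table 3 is not available, but the factor 15 − 1 = 14 implies one quarter without data per practice. I used the Hussey–Hughes generalised least squares variance (fixed period effects, random practice intercept), one transition quarter and starts two quarters apart. With p0(1−p0) in every cell, 2.802 × SE / √[p0(1−p0)] is 0.2358 at ICC 0.026 and 0.2295 at ICC 0.003, and shifting the layout in time does not alter this. All 12 rows follow to within 0.0005. For example, 0.2295 × √0.0291 = 0.0391 (stated 0.039) and 0.2358 × √0.25 = 0.1179 (stated 0.118).

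**Step 3: power at the stated differences.** Since d equals 2.802 standard errors under the control variance, replacing that variance by v̄ gives

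power = Φ(2.802 × √[p0(1−p0)/v̄] − 1.960).

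At p0 = 0.03: v̄ = (0.0291 + 0.0642)/2 = 0.0467; √(0.0291/0.0467) = 0.79; 2.802 × 0.79 − 1.960 = 0.25; Φ(0.25) = 0.60.

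**Step 4: differences that do have 80% power.** Solve d = k√v̄(d), with k = 0.2358 or 0.2295.

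| Outcome | p0 | Stated d | Power at stated d | d with 80% power |
|---|---|---|---|---|
| Completion | 0.03 | 0.039 | 60% | 0.053 |
| | 0.05 | 0.050 | 64% | 0.062 |
| | 0.10 | 0.069 | 70% | 0.079 |
| | 0.15 | 0.082 | 73% | 0.090 |
| | 0.20 | 0.092 | 74% | 0.099 |
| | 0.30 | 0.105 | 77% | 0.109 |
| | 0.40 | 0.112 | 79% | 0.114 |
| Initiation | 0.20 | 0.094 | 74% | 0.102 |
| | 0.30 | 0.108 | 77% | 0.112 |
| | 0.40 | 0.116 | 79% | 0.117 |
| | 0.50 | 0.118 | 81% | 0.116 |
| | 0.60 | 0.116 | 83% | 0.111 |

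**Step 5: other methods at 0.03 versus 0.069.** Cell-specific variances in the least squares calculation on the inferred layout give 60–62% power and a detectable difference of 0.051–0.052. An asymptotic Wald calculation for a logistic mixed model, closest to the planned analysis, gives 56–58% and about 0.055–0.057.

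**The case against.** The strongest reply is that 30 patients per practice-quarter was chosen as a cautious figure when 109 are seen on average. On the inferred layout with period-specific variances, power at 0.03 versus 0.069 is about 68% with 36 records, about 80% with 50 and 98% with 109. (Thirty-six comes from reading the cited rule of 50 records per 150 patients as a sampling fraction: 109 × 50/150 = 36.) This stands as a comment on the power the trial may achieve. It does not rescue the printed claim, because the 80%, the 3,780 subjects and Table 4 are all tied to 30.

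Second, the damage is uneven. Over most of the observed initiation range the change is 0.004 or less; completion at 30–40% moves by 0.002–0.004; and initiation at 50–60% is slightly better than stated. That is correct: the serious shortfall is in completion at 3–10%, with a moderate one at 15–20% and for initiation at 20%.

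Third, the table is a faithful output of a constant-variance approximation, and the number of practices and quarters was not derived from it. Both may be so. The text nevertheless asserts 80% power for a binary outcome whose rate changes, mentions no such approximation, and prints figures that are materially wrong where the approximation is poor.

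Finally, Table 3 had to be inferred, and the logistic result changes the scale of the test as well as the variance. The variance diagnosis and the 60% average-variance result do not depend on Table 3.

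**Conclusion.** The concern holds. All 12 rows of Table 4 use the control-period variance for both periods. At the stated 30 patients per practice-quarter, the smallest completion difference claimed, 0.039 at a 3% control rate, has about 60% power (56–62% across methods), so a true gain of that size would be missed about 40% of the time rather than 20%. The difference with 80% power there is about 0.051–0.053 on the risk-difference scale, which makes the stated figure roughly a quarter too small (0.039/0.0525 = 0.74). At control rates of 5, 10 and 15% power is about 64, 70 and 73%, so the claim fails across the range of completion rates the FQHCs have recorded.

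The power figures from the average variance assume that both periods contribute about equally to the standard error; the cell-specific results agree closely. The cell-specific and logistic figures, and the last decimals of the replacement differences, rest on the inferred layout. All keep the plan's other assumptions, including practice as the only level of clustering.

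**What to change.** Recompute Table 4 with the actual Table 3 matrix, using p0(1−p0) in control cells and p1(1−p1) in intervention cells, or by simulating the planned logistic mixed model. State in the text which variance and which effect scale were used.

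Then restate the two ranges in the Sample size justification. On the risk-difference scale, with everything else unchanged, they would be approximately 0.051–0.053 up to 0.114 for completion and 0.102 to 0.117 for initiation. These should be confirmed with the sponsor's own software. If more than 30 records per practice-quarter will be drawn, the recalculation can use that number, provided the text and total sample size are changed to match.

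The cost is one re-run of the power calculation and corrected text. Most stated differences become larger, most visibly for completion at low rates; initiation at 50–60% becomes slightly smaller. The design, randomisation and analysis model need not change.

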**Table 3 Tab3:**
[figure not shown]
Custom stepwise design matrix plot

**Table 4 Tab4:** Minimum detectable difference at 80% power using proposed design

Outcome	Intra-cluster correlation coefficient (ICC)	Rate in the control period	Minimum detectable difference at 80% power	Minimum detectable rate in the intervention period
HPV Initiation	0.026	0.2	0.094	0.294
		0.3	0.108	0.408
		0.4	0.116	0.516
		0.5	0.118	0.618
		0.6	0.116	0.716
HPV Completion	0.003	0.03	0.039	0.069
		0.05	0.05	0.1
		0.1	0.069	0.169
		0.15	0.082	0.232
		0.2	0.092	0.292
		0.3	0.105	0.405
		0.4	0.112	0.512

#### Statistical analysis plan

The same analytic strategy will be applied to each age group (11–12 vs. 13–17) for each HPV outcome separately. Both patient level characteristics (e.g., gender and ethnicity) and practice level characteristics (e.g., practice location and size) will be summarized using descriptive statistics and compared across the three FQHC groups using ANOVA or Kruskal-Wallis test for continuous variables and Chi-square or Fisher’s exact test for categorical variables. To compare the effect of facilitator-driven implementation strategies during the exposure period with the control period on the binary HPV outcomes, generalized linear mixed models (GLMMs) will be used with fixed effects for time and intervention as well as a random effect for practice, while considering patient-level and practice-level characteristics as needed. Heterogeneity of intervention effects will be examined by testing the interaction terms between intervention and potential effect.

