**Methods:**

This proposal considers the HPV vaccine as the evidence-based intervention and describes the rational and study design for “**TRU**sted h**E**alth **SY**stem implementatio**N** strat**EGI**es to increase vaccination (TRUE SYNERGI)”, a hybrid type 2 study that uses previously-piloted implementation strategies (i.e., practice facilitation, provider education, among others) to influence provider recommendations (implementation outcome) and practice-level vaccination rates (effectiveness outcome). To test whether these facilitator-driven implementation strategies influence our implementation and effectiveness outcomes, we will use a stepped-wedge cluster randomized trial and randomize three FQHCs (*n* = 9 practices, 3 per FQHC) to three clusters. We will conduct baseline assessments at each practice, which will provide data to assist the practice facilitator in engaging with the providers and leadership to develop a tailored implementation plan for each practice. In addition, we will employ theory-guided, qualitative methods, to assess the complexity associated with context and the recipients involved in the implementation of strategies in practices, along with sustainability.

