To address these gaps, our study team pilot tested TRUE SYNERGI in two Texas FQHCs, serving predominantly Latino/a adolescents and located in areas with high cervical cancer incidence rates for Latinas. Combining provider- and practice-level strategies using practice facilitation [63, 64], over a two-year implementation period, HPV vaccine initiation more than quadrupled (from 4 to 19%) in FQHC A and increased from 45 to 66% in FQHC B [65]. These preliminary data suggest external facilitation is a feasible approach for building the capacity in predominantly Latino serving FQHCs to select and implement provider- and practice-level strategies aimed at increasing vaccination rates. The study described in this manuscript builds on the pilot and aims to: 1) assess patient/parent-, provider- and practice-level characteristics (including vaccine hesitancy) that may influence the selection of implementation strategies, 2) use a participatory approach led by an external facilitator in each clinical practice to implement strategies, and 3) evaluate the implementation and identify factors that could influence future sustainability. We expect study findings to advance our understanding of implementation research in resource-limited practices that serve populations experiencing substantial health disparities, and to identify strategies that improve delivery and increase vaccine uptake. These findings could be disseminated to FQHCs nationwide that may share similar challenges in providing healthcare services to these patient populations and inform a future proposal focused on sustainability, an emerging area for equity focused implementation research.

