## Methods

### Overall design

The purpose of TRUE SYNERGI is to test the implementation and effectiveness of provider- and practice-level strategies aimed at increasing vaccination rates, first in a larger sample of practices and second, to improve our understanding of what combination of strategies influence provider recommendations and practice-level vaccination rates and under what conditions. We use a hybrid type 2 study design [66], focusing on understanding implementation aspects of an HPV vaccination focused set of strategies in a FQHC setting [66–68]. We are using a stepped-wedge, cluster randomized trial, among three predominantly Latino serving FQHCs with nine practice sites in Texas. We selected this design due to logistical, practical, and financial constraints in FQHC settings that make it more feasible for implementation to take place in stages [69] (See Table 1).

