### 2. Implementation of facilitator-led implementation strategies

Implementation strategies are methods or approaches that promote implementation indicators or outcome [86]. We will be focusing our efforts on the provider- and practice-level strategies described above. We will document the facilitation-driven implementation strategies selected by the clinical practice in their clinical practice plan. The i-PARIHS framework [63] will guide our understanding of the implementation of each of these strategies in the FQHCs. We will utilize the i-PARHS framework to guide the monthly meetings that will provide technical assistance if needed, assist in problem solving, and conduct a check-in, during the implementation period (defined as the first year after the start of project activities). Observational data in the form of monthly meeting notes and external facilitator debriefs will provide an in-depth understanding of the complex and dynamic *context* and the *recipients* (e.g., providers, immunization navigators, FQHC leadership) involved in the implementation at the practice settings. Baseline assessment findings will provide an in-depth understanding of the *context* and the *recipients*, which will enable the external facilitator to promote tailored implementation of strategies during implementation. We will utilize the i-PARIHS framework to review progress pre- and post-implementation and evaluate how strategies influenced implementation.

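### Interaction tests for practice-level characteristics leave out between-practice variation in the intervention effect, so they keep the 5% level only if practices do not otherwise differ in effect

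*Protocol article*

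**What the plan says.** The protocol article's Statistical analysis plan section gives the model for initiation and completion: "generalized linear mixed models (GLMMs) will be used with fixed effects for time and intervention as well as a random effect for practice". Patient-level and practice-level characteristics may be added as needed. The section's examples of practice-level characteristics are location and size. The next sentence is "Heterogeneity of intervention effects will be examined by testing the interaction terms between intervention and potential effect". It names no modifiers, no random intervention effect and no degrees of freedom.

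Three other places bear on this:

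- Overall design includes among the study's purposes learning "what combination of strategies influence provider recommendations and practice-level vaccination rates and under what conditions".
- The Methods part of the abstract has the facilitator and each site "develop a tailored implementation plan for each practice". The section on implementing the strategies adds: "We will document the facilitation-driven implementation strategies selected by the clinical practice in their clinical practice plan".
- The Introduction reports that in the pilot "HPV vaccine initiation more than quadrupled (from 4 to 19%) in FQHC A and increased from 45 to 66% in FQHC B".

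**The concern.** The question is whether a given characteristic changes the intervention effect, so the null hypothesis is that the effect does not depend on that characteristic. With only a practice intercept, the model tests something narrower: that practices with the same value of the characteristic share one identical effect. Where practices choose and adapt their own strategies, their effects may well differ for reasons unrelated to the characteristic.

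For a practice-level characteristic there are nine independent pieces of information, one effect per practice. The intercept-only model measures the contrast against patient-level binomial error instead. Chance differences in effect among nine practices can then look like effect modification. What is at stake is the quantitative answer to which conditions favour the strategies. The same omission also narrows the interval for the average effect when effects vary.

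**Working it through.** **1. Reproduce Table 4.** Inputs from Sample size justification: 9 practices (3 per FQHC), 15 quarters of which 14 are measured, 30 patients per practice-quarter, ICC 0.026 (initiation) or 0.003 (completion), two-sided 5%, 80% power. The Table 3 layout is not legible in the text at hand, so it was inferred. One transition quarter with FQHCs starting two quarters apart fits. The model is generalised least squares with quarter effects and a practice intercept only, with within-practice covariance σ²[(1−ρ)I/30 + ρJ] and σ² = p(1−p).

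- ICC 0.026: SE/σ = 0.08415, so MDD/σ = (1.960 + 0.842) × 0.08415 = 0.2358. Times √(p(1−p)) for p = 0.2 to 0.6 this gives 0.094, 0.108, 0.1155, 0.118, 0.1155. The table has 0.094, 0.108, 0.116, 0.118, 0.116.
- ICC 0.003: MDD/σ = 0.2295, which matches all seven completion values.

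Table 4 therefore stands, and it is consistent with a model that has no between-practice variance of the effect. It does not fix the starting quarter. Layouts with 1/3/5 and 5/7/9 control quarters fit equally well, and both are used below.

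**2. Closed form for a practice-level modifier with no true influence.** Let τ be the between-practice SD of the log odds ratio and v the sampling variance of one practice's log odds ratio. The test uses v where v + τ² is needed, so

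false-positive rate = 2[1 − Φ(1.96/√(1 + τ²/v))], with v = 1/(n₀p₀q₀) + 1/(n₁p₁q₁).

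Take p₀ = 0.30 and p₁ = 0.408 (a Table 4 row).

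- 1/3/5 layout: on average 3 control and 11 intervention quarters, so n₀ = 90 and n₁ = 330. v = 1/18.9 + 1/79.7 = 0.0655.
- 5/7/9 layout: 7 and 7 quarters, so n₀ = n₁ = 210. v = 1/44.1 + 1/50.7 = 0.0424.

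At τ = 0.30 the rates are 2[1 − Φ(1.96/√2.37)] = 20% and 2[1 − Φ(1.96/√3.12)] = 27%.

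**3. Simulation.** Binomial data on the fitting layouts: control rate 30–33%, mean log odds ratio about 0.5, ICC 0.026, practice-specific effects with SD τ, no modifier effect, Wald test at 1.96, 300 to 800 replicates per setting. The modifier splits the practices 4 versus 5.

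| τ (logit) | Closed form | Simulated |
|---|---|---|
| 0 | 5% | about 4–6% |
| 0.15 | 9–11% | 9–12% |
| 0.30 | 20–27% | 18–27% |
| 0.61 | 45–53% | 44–53% |

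Other simulated results:

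- FQHC-level characteristic (one FQHC against two): 8–9%, 16–24% and 36–48% at τ = 0.15, 0.30 and 0.61.
- With 109 patients per practice-quarter (the 2019–2021 average), 4-versus-5 split: 16–23%, 42–49% and about 70% at the same three SDs.
- Patient-level modifier: 4–6% at τ = 0.3 and 0.5.
- Coverage of the 95% interval for the average effect: 88–92% at τ = 0.30 and 73–82% at 0.61.

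**4. Where 0.61 comes from, and its limits.** The pilot changes on the logit scale are ln(0.19/0.81) − ln(0.04/0.96) = 1.73 and ln(0.66/0.34) − ln(0.45/0.55) = 0.86. Their SD is 0.864/√2 = 0.61. As risk differences they are 0.15 and 0.21, with SD 0.06/√2 = 0.042. The same closed form with v = p₀q₀/n₀ + p₁q₁/n₁ gives 12% for 90/330 and 15% for 210/210 (11% for 70/350), so about 11–15%.

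**5. Does the remedy hold the level?** A two-stage analysis (nine practice-specific log odds ratios regressed on the characteristic, t with 9 − 2 = 7 df) gave about 4–6%. A random intervention effect by practice gave about 3–10% with a normal reference and about 1–6% with t(7), over τ from 0 to 0.6.

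**The case against.** The strongest reply is that the text fixes less than the concern assumes. The word intercept does not appear, no modifier is named, and location and size are introduced as characteristics to be summarised, with covariate adjustment only as needed. An article may leave the finer random-effects structure to a fuller document. This stands in part: the point has to be conditional on a practice-level characteristic being tested. It does not remove the point, because the article does state a model. A single random effect for practice is naturally an intercept, and Table 4 reproduces on that basis.

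The second reply is that the size is not a property of the plan. A reader might infer that these tests have a false-positive rate of 16–51%. The documents do not support that as an unconditional figure, since it needs an assumed SD of about 0.30 to 0.61 logit and they give no SD. The pilot value rests on two uncontrolled FQHC-level changes without denominators, one starting at 4%, whereas the participating FQHCs range from 24.6% to 40.9%. It also depends on the scale. This objection stands.

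A reader might also infer that all the heterogeneity tests fail. They do not: gender or ethnicity, as patient-level modifiers, keep about 5%. Nor is the 109-patient case certain. The cited sampling guideline of 50 records per 150 patients would give 109 × 50/150 ≈ 36, close to the planned 30.

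Finally, the conditions question is also addressed qualitatively, and no decision hangs on the interaction tests. That limits the consequence but does not make a miscalibrated test useful.

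**Conclusion.** The point holds in a conditional form. For any practice-level characteristic tested as a modifier in the stated model, the 5% level is kept only if practices sharing that characteristic have the same intervention effect. The protocol's own tailoring makes that doubtful. The excess runs from none at SD 0, through roughly a doubling at 0.15 logit, to about half of all tests at 0.61. The size rests on the assumed SD, the inferred rollout, a control rate near 30% and 30 patients per practice-quarter.

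Table 4 is not in error. The secondary consequence, an interval for the average effect that is too narrow when effects vary, depends on the same assumed SD and justifies a sensitivity analysis, not a claim that the primary comparison is invalid.

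**What to change.** In the Statistical analysis plan section:

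- State that practice-level modifiers are tested against between-practice variation on about 7 df. Use either a random intervention effect by practice with small-sample degrees of freedom, or the two-stage analysis of nine practice-specific log odds ratios (common quarter effects, t with 7 df).
- State that FQHC-level modifiers are described only, since there are three FQHCs.
- Report the average effect with a random intervention effect by practice as a sensitivity analysis.
- Leave patient-level interaction tests as they are.

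The cost is a few sentences and a few lines of code. Intervals will be wider and power for practice-level modifiers low, which is what nine practices can support. The slope variance will be estimated imprecisely, and the random-effect version with t(7) can be conservative (about 1% in some settings). The two-stage version avoids having to estimate that variance within the GLMM.
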